#### Low fat diet

The LFD group will follow the same structure as the MedDiet arm with three face to face consultations at baseline, 6 weeks (mid intervention) and 12 weeks (end of intervention). There will also be the same number of phone call follow ups at weeks 2, 4 and 9. The education and resources provided will be determined by the APD running the consultations and these will involve what would normally be provided in a typical outpatient dietetic consult. This will include based on the Australian Guide to Healthy Eating with an emphasis on portions, low fat options and cooking methods. Participants will also be given a supermarket gift voucher to purchase some of the suggested food items.

Breakfast is also provided on the day of all face to face appointments (Jalna © and Carmen’s ©).

### Outcome measures

The outcome measures collected and their parallel timelines are displayed in Table 1. Patient information including demographic data, smoking status, medication and supplement consumption are taken at baseline and checked at each face-to-face appointment for changes.

### Anthropometry

Weight, height, waist circumference, hip circumference, neck girth and blood pressure will be taken using standard procedures, in duplicates by a trained researcher at all face to face appointments.

Body Composition will be assessed using Seca© bio electrical impedance analysis scales at all face to face appointments. DXA scans using a Hologic© machine will a be used to assess body composition in a consenting volunteer subset of participants.

### Dietary and lifestyle

Three day food diaries including 2 weekdays and 1 weekend, a Food Frequency Questionnaire (FFQ) and the PREDIMED Checklist (a measure of dietary compliance specifically designed to measure key elements of the diet administered for each study arm) will be collected from participants at baseline, mid intervention and post intervention to assess dietary compliance relative to the recommendations provided. The Active Australia questionnaire will monitor changes in physical activity. The Short Form Health Survey (SF- 36) will be used to collect quality of life data. All questionnaires will also be administered at 6 and 12 months to observe any sustained behaviours and thus the ability to maintain the recommended changes and any metabolic benefits.

### Imaging

MR-S images will be taken by a qualified radiographer using a Simmens© MRI machine and will be used as the gold standard to monitor changes in the percentage of intrahepatic lipids in the liver. Following a minimum 2 h fast, Transient Elastography (FibroScan®) will be taken in patients to monitor changes to liver fibrosis throughout the study duration.

### Laboratory

Pathology blood samples will be prepared by the nominated laboratories or researchers according to standard protocol. Once prepared samples will be processed and plasma will be stored in −80 °C freezers at the Department of Gastroenterology, The Alfred Hospital Prahran and the Department of Dietetics and Human Nutrition, La Trobe University Bundoora campus until batch analysis of assays are performed.

Plasma fatty acids and urinary metabolites both represent key markers of dietary compliance and will be processed and analysed at La Trobe University. Peripheral blood mononuclear cells (PBMCs) will be utilised to assess metabolomics investigating the genetic variations in genotype/phenotype and will be processed and analysed using polymerase chain reaction (PCR) at La Trobe University. A buccal swab will also be taken at baseline for all participants to assess the DNA profile of the study population.

### Data management

The key researcher at each site will be responsible for storage of hard copies of coded case report forms and questionnaires which will be in kept in secure filing cabinets. All electronic data will be saved in a password protected database. Participants who are interested in the study results will be flagged and individual and overall data will be disseminated at the conclusion of the study.

### Study integrity

Approval to carry out the study was obtained from La Trobe University, the Alfred, Eastern Health, Royal Melbourne Hospital’s research and ethics committee and ethics review is currently underway at St Vincent’s. Written informed consent will be obtained from all participants. This randomised control trial protocol has been designed with close consideration of the CONSORT guidelines [21]. In addition this study protocol has been reviewed by the La Trobe University Research Focus Area board who provided seed funding for the commencement of this trial.

### Sample size

We aim to recruit 47 participants per arm (94 in total) allowing for a 20 % drop out rate over 12 months. This sample size has been calculated with 80 % power to detect a between-group difference in HOMA-IR of 1.0 unit or more at the end of the 12 week duration, with the assumed standard deviations for control and intervention groups of 0.118 and 0.141, respectively. The assumed mean difference and group-specific standard deviations were calculated based on the following past studies: Ryan [16], Esposito [22], Esposito [23] and Elhayany [24].

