### Inclusion criteria

Participant eligibility includes those aged >18 years who have a body mass index (BMI) between 20 and 39.9 kg/m^2^. Participants must have a diagnosis of NAFLD determined by routine ultrasound or biopsy; insulin resistance based on a HOMA IR score of >2; and at least one elevated serum ALT level (>20 U/L female, >30 U/L male) during the past 6 months. Eligible participants must have no evidence of another form of liver disease.

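### The printed sample-size inputs do not give 47 per arm at 80% power, so the trial's power for a 1.0-unit HOMA-IR difference cannot be determined from the protocol

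*Protocol article*

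**What the plan says.** All the inputs but the significance level are in the Sample size section of the protocol article. Recruitment: "We aim to recruit 47 participants per arm (94 in total) allowing for a 20 % drop out rate over 12 months". Target: "80 % power to detect a between-group difference in HOMA-IR of 1.0 unit or more at the end of the 12 week duration". Variability: "assumed standard deviations for control and intervention groups of 0.118 and 0.141, respectively". The section attributes the difference and the SDs to four earlier studies.

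The Statistical analysis section sets a 5% significance level without saying one- or two-sided, and plans linear mixed-effect models for quantitative endpoints such as HOMA-IR. The Study design section defines the primary endpoint as a one-unit reduction in HOMA-IR over 12 weeks, so the raw scale is intended. Eligibility sets only a lower bound on the same variable: "insulin resistance based on a HOMA IR score of >2".

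**The concern.** The paragraph prints a complete calculation, so it can be checked without any outside source. A 1.0-unit difference against SDs of 0.118 and 0.141 is a standardised effect far beyond anything that would call for 47 per arm.

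The SDs also look wrong for raw HOMA-IR. If they were between-person SDs, 95% of an arm would lie within about ±0.23 units (1.96 × 0.118) or ±0.28 units (1.96 × 0.141) of its mean. The population is bounded only from below and, because randomisation is stratified by diabetes status, mixes people with and without diabetes.

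This paragraph is the only justification given for the size of the trial. If its inputs cannot have produced its answer, nobody can tell whether the trial is well or poorly powered for its one-unit target, and the 80% figure would be carried into the trial report.

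**Working it through.** **Inputs.** From Sample size: difference 1.0; SDs 0.118 and 0.141; power 80%; loss 20%; 47 per arm. From Statistical analysis: 5% level, taken here as two-sided. Results from the second step on are for an unadjusted t-test.

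**1. The plan's own figure, normal approximation.**

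n per arm = (SD₁² + SD₂²) × (1.960 + 0.842)² / difference²

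= (0.0139 + 0.0199) × 7.85 / 1.0² = 0.27, which rounds up to 1.

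A one-sided test (0.21) or 90% power (0.36 two-sided) also rounds up to 1.

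**2. Small-sample check.** The average SD is √[(0.118² + 0.141²)/2] = 0.130, so the standardised difference is 1.0/0.130 = 7.7. A pooled t-test at its minimum of 2 per arm has 95% power. Allowing for loss, 2/0.8 = 2.5, so 3 per arm. That is the like-for-like figure against 47, which already includes loss. (A Welch test at 2 per arm has 94% power by the noncentral-t formula but only 65% by simulation. It would need 3 per arm, or 4 after loss. This does not matter for the conclusion.)

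**3. Power at the planned size.** 47 × 0.8 = 37.6. With the printed difference and SDs, power at 37 to 47 per arm is essentially 100%, not 80%.

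**4. What would have to be different at 37 per arm and 80% power.**

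- With the printed SDs, the detectable difference is about 0.086 units.
- With the 1.0-unit difference, the common SD must be about 1.5 (1.515). That is 1.515/0.141 = 10.7 to 1.515/0.118 = 12.8 times the printed values.

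**5. Readings that might explain 47.**

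| Reading | Per arm before loss | After 20% loss |
|---|---|---|
| Tenfold slip, 80% power | 28 | 28/0.8 = 35 |
| Tenfold slip, 90% power | 37 | 37/0.8 = 46.25, so 47 |
| Printed SDs are standard errors from past groups of 20 to 100 (assumed sizes), 80% power, normal formula | 6 to 27 | 8 to 34 |

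The tenfold slip can be SDs of 1.18 and 1.41 with a difference of 1.0, or the printed SDs with a difference of 0.10; the ratio is the same. It reaches 47 only at 90% power, which contradicts the stated 80%.

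**6. Illustrative power for 1.0 unit.** The SDs below are assumptions, not figures from the protocol.

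| Common SD | 37 per arm | 47 per arm |
|---|---|---|
| 1.0 | 99% | over 99% |
| 1.5 | 81% | 89% |
| 2.0 | 56% | 67% |
| 2.5 | 40% | 48% |
| 3.0 | 29% | 36% |

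**The case against.** The non-reproduction itself cannot be answered. Sidedness, rounding and the way loss is added do not close a gap between 3 and 47, and the article names no log scale, standard error or other variance. The objections that stand concern what may be concluded from it.

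- **Retention.** The 20% loss is stated over 12 months, but the primary comparison is at 12 weeks. Evaluable numbers then lie between about 37 and 47 per arm, and the article does not say where. At SD 2.0 that alone moves power from 56% to 67%.
- **Analysis.** The power table is for an unadjusted comparison of two means, whereas mixed models are planned and fasting blood is taken at baseline, 6 and 12 weeks. If baseline HOMA-IR is used and correlates 0.5 to 0.7 with week 12 (an assumption), power at SD 2.0 and 37 per arm is 69% to 84%. The table is an illustration, not the trial's power.
- **Cause.** A tenfold slip at 90% power fits 47 and, read as SDs of 1.18 and 1.41, keeps the one-unit target. Under it power would be better than stated. Standard errors or log-scale SDs are also possible. None can be confirmed, because the source studies are not at hand.

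A reader might infer that 94 participants are too few. The document does not support that: under the assumed SDs, power runs from about 29% to over 99%. A reader might also infer that a null result could not count against a 1.0-unit effect. That too goes beyond the evidence, because the observed confidence interval decides it, not the planned power.

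**Conclusion.** The sample-size statement is wrong as written. Its difference, SDs and power are mutually incompatible with 47 per arm: they call for 2 per arm by t-test, or 3 after loss. At least one of the three is misstated, and the document does not show which.

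The real power for the one-unit target therefore cannot be determined from the protocol. It depends on the true SD, on retention at week 12 and on how far the planned model gains from baseline and repeated measurements. The arithmetic assumes a two-sided 5% level; a one-sided test does not change the conclusion. The SD of about 1.5 is solved backwards from the sample size and is not evidence of what the SD is.

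**What to change.** Recheck the figures taken from the four source studies, including whether they were standard errors or on a log scale, and rewrite the Sample size paragraph so that it gives:

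- the difference and the SDs on the same scale, with the SDs that the sources actually support;
- the sidedness of the test and the power used;
- the retention assumed at week 12, separately from the 12-month loss.

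Keep N = 94 and restate the power it delivers for the 1.0-unit target. Show power over a range of SDs, as in the second table above, labelled as an unadjusted illustration that baseline adjustment or the mixed model could improve. Do not enter an SD of 1.5 unless the source studies support it. If the scale or the difference changes, reconcile the paragraph with the one-unit primary endpoint in the Study design section.

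Cost: one paragraph and no extra patients. The restated power may turn out more or less favourable than 80%.

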### Statistical analysis

Intention-to-treat (ITT) principle will be used to analyse and compare the intervention and control groups. As per ITT principle, for the purpose of statistical analyses, all participants will retain their randomised (allocated) group, regardless of the actual treatment received. T-test will be used to examine the effectiveness of randomisation by comparing baseline characteristics across the two groups. If data are not normally-distributed, nonparametric Kruskal-Wallis test will be used instead.

For quantitative endpoints (e.g., HOMA-IR), linear mixed-effect models will be used to compare the intervention and control group. If normality assumption is not fulfilled, suitable transformation (e.g., log) will be performed on the response variable to ensure the assumption is met. For binary endpoints (e.g., improvement in lipid profile >20 %), mixed-effect logistic regression for longitudinal data will be used. In both cases, data from all participants, including those who withdraw after baseline, will be retained for analyses. When required, potential confounders (e.g., age, BMI) will be adjusted for by including them as additional covariates in the models.

When multiple hypothesis testings are performed (e.g. with SNP data), Holm’s procedure (Holm, 1979) will be used to control the familywise error rate. All statistical analyses will be performed using 5 % significance levels. R version 3.1.1 (www.r-project.org) and STATA version 12 will be used to conduct the statistical analyses.

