## Methods

### Study design and outcome measures

This is a 12 week, multi-centre, parallel, randomised controlled trial of a Mediterranean diet versus a Low Fat Diet (LFD) in patients with NAFLD on insulin resistance, hepatic steatosis and Metabolic Syndrome (MetS) risk factors. Enrolment of 94 participants will occur at four sites across metropolitan Melbourne, Australia: Alfred Health, St Vincent’s Hospital, The Royal Melbourne Hospital and Eastern Health. Both the recruitment and intervention are anticipated to take place over a 24 month period. Participants will undergo stratified randomisation according to gender and diabetes status, into either the intervention; MedDiet or the LFD arm. The primary endpoint is the reduction of one unit of homeostasis model assessment of insulin resistance (HOMA-IR) over the 12 week intervention period. Secondary outcome variables include a reduction in intrahepatic lipid accumulation measured by Magnetic Resonance –Spectroscopy (MR-S), normalisation or improvement of alanine aminotransferase (ALT), lipid profile, liver stiffness as measured by transient elastography (Fibroscan®), inflammatory cytokine markers, quality of life measures, anthropometry and body composition, biomarkers of dietary intake and blood pressure.

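### The scale of the primary HOMA-IR analysis is left to a normality check, so the effect tested may not be the 1.0-unit difference that the trial defines and powers

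*Protocol article*

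**What the plan says.** Three sections of the protocol article bear on the scale of the primary analysis.

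- Study design and outcome measures puts the endpoint in units: "The primary endpoint is the reduction of one unit of homeostasis model assessment of insulin resistance (HOMA-IR) over the 12 week intervention period".
- Sample size does the same: "80 % power to detect a between-group difference in HOMA-IR of 1.0 unit or more at the end of the 12 week duration", with "assumed standard deviations for control and intervention groups of 0.118 and 0.141, respectively". The size is 47 per arm, 94 in all, with 20% drop-out allowed for.
- Statistical analysis assigns quantitative endpoints to linear mixed-effects models and gives HOMA-IR as the example. It adds that if the normality assumption fails, a "suitable transformation (e.g., log) will be performed on the response variable to ensure the assumption is met".

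Inclusion criteria requires "insulin resistance based on a HOMA IR score of >2" and states no upper limit for HOMA-IR.

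**The concern.** The endpoint and the power statement are fixed in units, but the analysis scale is not. Whether the primary result is a difference in units, a ratio of geometric means or something else depends on how the outcome data look, and log is only an example of what may be used. A unit difference and a ratio are different estimands. They can give different p-values, and a 1.0-unit target translates to a different ratio at each control level. If the switch occurs, the trial reports a quantity that it did not define as its endpoint and did not power.

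The situation is foreseeable. HOMA-IR is positive, and entry is bounded below and not above, so right skew is a reasonable expectation. That is an assumption, since the article gives no distribution. The scale can be chosen now.

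**Working it through.** **1. The plan's own figure.** Inputs from Sample size: difference 1.0, SDs 0.118 and 0.141. The level is 5% (Statistical analysis), taken as two-sided because the article does not say.

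- Root mean square SD = √[(0.118² + 0.141²)/2] = 0.130.
- n per arm = 2 × [0.130 × (1.96 + 0.84)/1.0]² = 0.27, that is 1 per arm, or 2 after 20% drop-out.

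The stated 47 per arm is not reproduced. With 47 × 0.8 ≈ 38 evaluable per arm, 80% power for 1.0 unit implies an SD of √(38/2)/2.80 = 1.56. This is a separate defect. It matters here only because it leaves no usable SD to carry to another scale.

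**2. What 1.0 unit becomes on the log scale.** For control mean c, a 1-unit reduction is the ratio r = (c − 1)/c. With log-SD σ and 38 evaluable per arm:

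- power = Φ(|ln r| / (σ√(2/38)) − 1.96)
- n per arm for 80% power = 2 × (2.80σ/|ln r|)²

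The article gives neither c nor σ, so both are assumptions. At σ = 0.5:

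| Assumed control mean | Ratio | Power, 38 per arm | Evaluable n per arm for 80% |
|---|---|---|---|
| 3 | 0.67 | 94% | 24 |
| 4 | 0.75 | 71% | 48 |
| 5 | 0.80 | 49% | 79 |
| 6 | 0.83 | 36% | 119 |

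With σ from 0.4 to 0.6, power runs from 99% to 84% at control mean 3 and from 51% to 26% at control mean 6. The stated 80% has no fixed meaning once the scale changes.

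**3. How often the scale would change.** Two simulations with assumed log-normal data and a Shapiro-Wilk check on the residuals at 5%, as a stand-in for the unspecified check:

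- Two-group comparison, 38 per arm, no baseline adjustment: the analysis moves to log in about 42%, 74%, 92%, 98% and over 99% of trials at log-SD 0.2, 0.3, 0.4, 0.5 and 0.6.
- Baseline-adjusted comparison, 37 per arm, baseline median 3.5 and log-SD 0.5 truncated at >2, within-person log-SD 0.25 to 0.45: it moves to log in about 70-92%.

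**4. Whether the scale matters to the conclusion.** In the baseline-adjusted simulation with an assumed 22% reduction, raw and log analyses fall on opposite sides of the 5% level in roughly 3-17% of trials.

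The two scales also test different null hypotheses. For log-normal data the geometric mean is the arithmetic mean times exp(−σ²/2). Equal arithmetic means with log-SDs 0.4 and 0.6 therefore give a geometric mean ratio of exp[(0.16 − 0.36)/2] = 0.90. In that setting, with 38 per arm, the raw test rejects in 5.4% of trials and the log test in 13.4%.

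**5. What the rule does not damage.** When both arms share one distribution, type I error of checking and then choosing is 5.0-5.3% in the two-group simulation and also near 5% in the baseline-adjusted one. Its power is within 1 point of an analysis that always uses log.

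**The case against.** The strongest reply is that the rule works. It moves to log in the situations where log is the better scale, keeps the type I error, and gives up almost no power against fixing log beforehand. That stands, and it limits the point to the estimand and its match with the endpoint and the power statement.

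A second reply is that an article leaves the normality criterion, the exact transformation and the back-transformation to an analysis plan that is not shown. That stands for those details. It does not cover the conditional sentence itself, which is printed here, applies to HOMA-IR by name, and does not fit the unit-based endpoint and power statement in the same article.

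Third, the skew argument has limits. The >2 criterion truncates values at entry, not week-12 residuals. The BMI limit of 39.9 and the exclusions for HbA1c above 8% and insulin-dependent diabetes may shorten the upper tail. The switch is therefore likely under the assumptions shown, not certain.

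A reader might infer more than the document supports:

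- That the check is made on unblinded data. The article does not say when, by whom or on what data normality is assessed; a check pooled over arms before allocation is revealed fits the text equally well.
- That the rule inflates type I error or costs power. The simulations show neither.
- That the scale rule explains why 47 per arm cannot be reproduced. The calculation already fails in raw units.

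**Conclusion.** The point holds as a mismatch. The primary endpoint and the power statement are in HOMA-IR units, while the stated analysis rule allows the estimand to become a ratio, or neither a ratio nor a unit difference, after outcome data are seen. Under assumed log-normal data the change would occur in most trials, except at the smallest spread tried (42% at log-SD 0.2). The choice of scale would alter significance in roughly 3-17% of trials with a 22% effect. These sizes rest on the assumed distribution, spread and effect and on Shapiro-Wilk as the check; the article supplies none of them. The mismatch itself follows from the text alone. It should be corrected, and correcting it is cheap.

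**What to change.** - Name one primary scale for HOMA-IR at week 12 in advance. One option is log(HOMA-IR) with log baseline as covariate, reported as a ratio of geometric means with its 95% CI.
- Keep the other scale as a named supportive analysis; if log is primary, this is the raw-unit difference with robust standard errors.
- Delete the conditional transformation rule for the primary endpoint.
- If log is chosen, reword the one-unit endpoint and state the targeted ratio. Give the control mean and log-SD as explicit assumptions, shown over a range, because the article has no figure for either.

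Fixing the raw scale in advance would also remove the mismatch and would keep the endpoint as worded.

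The cost is mostly wording. On the log scale the headline becomes a percentage difference rather than units, and the power statement must be restated. That restatement may show that the planned size is ample or too small, depending on the assumed control mean.

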### Study procedure

#### Screening assessment

Prospective participants will undergo a thorough screening questionnaire administered face-to-face by a trained researcher. Once considered eligible, participants will undergo computer generated randomisation stratified to gender and diabetes status completed by the statistician. Participants will be allocated into either the LFD or the MedDiet arm of the study and booked in for their initial appointment.

Randomisation will control for equal distribution of key characteristics that may confound between group comparisons and will be assessed by analysis of baseline data.

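### The primary model is not committed to the randomisation strata or to a stated use of baseline HOMA-IR, and its only covariate rule is open-ended

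*Protocol article*

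**What the plan says.** All references are to the protocol article.

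- **Design.** Under Study design and outcome measures: "Participants will undergo stratified randomisation according to gender and diabetes status". The Screening assessment section repeats it: "participants will undergo computer generated randomisation stratified to gender and diabetes status completed by the statistician".
- **Primary model.** Under Statistical analysis: "For quantitative endpoints (e.g., HOMA-IR), linear mixed-effect models will be used to compare the intervention and control group". No fixed effects are listed beyond the group comparison.
- **Covariates.** The only rule is: "When required, potential confounders (e.g., age, BMI) will be adjusted for by including them as additional covariates in the models".
- **Baseline tests.** Also under Statistical analysis: "T-test will be used to examine the effectiveness of randomisation by comparing baseline characteristics across the two groups", with Kruskal-Wallis as the fallback for non-normal data. The Screening assessment section says: "Randomisation will control for equal distribution of key characteristics that may confound between group comparisons and will be assessed by analysis of baseline data".
- **Who stays in.** Under Statistical analysis: "data from all participants, including those who withdraw after baseline, will be retained for analyses".

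**The concern.** Two variables were judged important enough to stratify on. An analysis that respects the design carries them in the model, because otherwise the standard error ignores variance that the stratification has already balanced. The article does not commit to this, and the covariates it gives as examples are two different ones.

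Baseline HOMA-IR is normally a strong predictor of week-12 HOMA-IR, yet its role is not stated.

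The covariate rule leaves open when adjustment is needed, which variables qualify, and whether the choice is made before or after the data are seen. Several primary models could therefore all be called consistent with the protocol. The rule also does not say baseline BMI. Weight is measured at every visit in Table 1, so a post-randomisation BMI is not excluded, and adjusting for it would change the effect being estimated.

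Finally, the baseline tests are given a purpose they cannot serve. Under valid randomisation any baseline difference is due to chance, so a p-value says nothing about whether randomisation worked.

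**Working it through.** **Inputs from the article.** 47 per arm with 20% dropout, so 47 × 0.8 = 37.6, about 38 completers per arm (76 in total). Target difference 1.0 HOMA-IR unit, 80% power, 5% level (two-sided assumed).

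**Assumptions, because the article gives no figures.** Share of HOMA-IR variance explained by the strata, R² = 0.1, 0.2, 0.3. Baseline to week-12 correlation ρ = 0.5 to 0.7. The SDs in the Sample size section (0.118 and 0.141) do not lead to 47 per arm, which is a separate matter. For illustration I use the SD that gives 80% power with 38 per arm: 1.0 / [√(2/38) × (1.960 + 0.842)] ≈ 1.556.

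**Step 1: which contrast is planned?** The text supports two readings. The Sample size section speaks of a between-group difference at the end of 12 weeks. The Study design section speaks of a reduction over the 12-week period, and retaining people who withdraw after baseline suggests that baseline is one of the repeated responses. Both are worked through.

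**Step 2: week-12 comparison without baseline or strata.** The true size of a nominal 5% test is about 2 × [1 − Φ(1.96/√(1 − R²))]:

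- R² = 0.1: 0.039
- R² = 0.2: 0.028
- R² = 0.3: 0.019

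**Step 3: change-from-baseline contrast.** Strata effects that are constant over time cancel in the change, so the step 2 formula no longer applies. Simulation with 76 completers, stratified randomisation and within-stratum ρ = 0.5 gives:

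| Quantity | R² = 0.1 | R² = 0.2 | R² = 0.3 |
|---|---|---|---|
| Type I error, week-12 only | 0.040 | 0.030 | 0.018 |
| Type I error, change from baseline | 0.055 | 0.050 | 0.051 |
| Power, change from baseline | 0.82 | 0.87 | 0.91 |
| Power, baseline and strata adjusted | 0.91 | 0.94 | 0.96 |

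A separate simulation (8,000 null runs, blocks of 4) put the type I error of the model with baseline and both strata at 0.050, 0.049 and 0.051.

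**Step 4: gain from baseline adjustment.** With common variance σ², the per-arm variance is:

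- week-12 only: σ²
- change: 2σ²(1 − ρ)
- baseline-adjusted: σ²(1 − ρ²)

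The ratio of adjusted to change is (1 − ρ²) / [2(1 − ρ)] = (1 + ρ)/2, which is 0.75 at ρ = 0.5 and 0.85 at ρ = 0.7. The ratio of adjusted to week-12 only is 1 − ρ², which is 0.75 and 0.51. The second pair matters only if the week-12 comparison without baseline is what is planned.

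**The case against.** The strongest reply is that the article is silent on model terms and excludes nothing. Age and BMI are given only as examples, and an unseen analysis plan may name the strata. This stands against a tempting stronger reading, that the models leave out gender, diabetes status and baseline HOMA-IR. The documents do not support that. The list is open, and keeping baseline-only participants suggests that baseline is already in the model as a response.

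A second reply also stands: the conservative type I error belongs to a week-12 comparison without baseline. Under a change contrast it is essentially absent, provided the strata effects are stable over time.

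A third stands in part. A reader might infer that covariates enter only after a significant baseline test. The Screening assessment section links baseline analysis to possible confounding, and the covariate sentence speaks of confounders. But no sentence makes adjustment depend on a p-value, so this remains an inference.

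These replies do not remove the point. The article is not merely silent on covariates. It states a rule, and that rule is discretionary, so any plan that pre-specifies the model would have to replace it. It also assigns the baseline tests a purpose they cannot meet.

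**Conclusion.** The point holds as one of precision and pre-specification. The protocol stratifies on two factors, commits the primary model to neither, does not say how baseline HOMA-IR is used, and leaves further adjustment to judgement. It should not be read as a claim of bias or of an inflated type I error from omitting the strata.

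Size depends on the reading. For a week-12 comparison without baseline, the test runs at about 4%, 3% or 2% instead of 5%. For a change contrast, the level is about right. Baseline adjustment still reduces variance to 75%–85%, and in the simulation power rises from 0.82/0.87/0.91 to 0.91/0.94/0.96 with baseline and strata in the model. All of this rests on assumed R² of 0.1–0.3 and correlations of 0.5–0.7 (0.5 in the simulation), on strata effects that are constant over time, and on an illustrative SD. The discretion over the primary model rests on none of these and follows from the text alone.

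**What to change.** Replace the conditional covariate sentence in Statistical analysis with:

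> All primary and secondary models include gender, diabetes status and the baseline value of the outcome (as a covariate, or as a response with baseline means constrained equal across arms so that baseline-only participants stay in). Age and baseline BMI enter one pre-specified sensitivity model.

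The constrained-means form fits better with the stated wish to retain participants who withdraw after baseline.

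Delete the sentences on baseline t-tests and Kruskal-Wallis tests, and report baseline characteristics descriptively by arm.

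The cost is protocol and analysis-plan wording, plus two degrees of freedom for the strata and one more if baseline enters as a covariate. Gender and diabetes status are already needed for randomisation, and the other variables are already collected.
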